**Methods:**

A cluster randomized controlled trial will randomly allocate 10 wards from four hospitals in Nanchang to either an intervention group (*N* = 5) or a usual care group (*N* = 5). At least 27 participants will be recruited from each ward and the estimated sample size will be 135 patients in each group. The intervention includes individualized self-care education prior to discharge and 6-month follow-up in community health service centers. Health professionals from both hospitals and community health service centers will be resourced to collaborate on the implementation of the postdischarge interventions that reinforce self-care. The primary outcome is systolic blood pressure at 6-month follow-up adjusted for baseline value. Secondary outcomes are self-care knowledge, treatment adherence, HbA1c and lipid levels, quality of life, the incidence of adverse events and the incidence of unplanned hospital readmission at 6-month follow-up adjusted for baseline value. A multilevel mixed-effect linear regression model will be used to compare the changes in health outcomes between the intervention and usual care groups.

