### Outcome measures

#### Primary outcome

The primary outcome is systolic blood pressure at 6-month follow-up adjusted for baseline value. At each measurement point, blood pressure will be measured three times at 5-min intervals on the participant’s right arm in a sitting position. The average of the three blood pressure readings will be calculated as the final BP reading for each group at each time point, which minimizes measurement error.

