### Sample size

The sample size calculation is based on the primary outcome and is estimated on the basis of an earlier randomized controlled trial study in relation to hypertension management for diabetic patients [36]. In this earlier study, the researchers found a 7.3 mmHg significant reduction in systolic blood pressure (SBP) with a standard deviation of 12.1 mmHg and an intraclass correlation coefficient (ICC) of 0.05 in the intervention group [36]. Since randomization in our study will be done by wards (clusters), the sample size has been adjusted to take into account the design effect. Our study is designed to have 80% power to detect a difference of 7.3 mmHg SBP between the group means when the standard deviation is 12.1 mmHg. This assumes that a sample size of five clusters per group with 25 participants per cluster will complete the study and the ICC is 0.05, giving a design effect of 1.48. The ICC also reflects the situation that the hospitals in the study are from the same city under the same hospital administration standard; therefore, each cluster is unlikely to differ from the others with respect to the variable of interest. Each cluster will be of equal size. Assuming an attrition rate of 10%, we would require 27 participants per cluster. In total, 10 clusters with 270 participants will be recruited.

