### Statistical methods

Statistical analysis will be performed using Statistical Package for Social Science (SPSS) version 23 and STATA software version 14. To test the effectiveness of the intervention on the primary and secondary outcomes, a multivariate multilevel mixed-effects linear regression model will be used to analyze outcomes. This is due to the hierarchical structure of the data and is based on the consideration of the correlations between participants’ repeated measurements over time. Because the participants are nested within hospital wards, we will fit a three-level mixed model with random intercepts at both the cluster and the participant-within-cluster levels. Thus, models will account for the clustering in wards, participants within clusters and over time using the *mixed* command. Wards and participants within wards will be treated as random effects. The main effects will be group (intervention or comparison), time (baseline, 3 and 6 months) and group × time interaction. A small-sample correction to the restricted maximum likelihood estimator will be used to improve the inference for the fixed parameters and is available in STATA *mixed* command. Models will be adjusted by baseline value and confounders that include age, gender, body mass index (BMI), duration of hypertension, duration of diabetes, smoking status and education level [37, 38]. A univariate model will also be used for unadjusted estimates. The level of significance will be set at *p* < 0.05. Where appropriate, 95% confidence intervals (95% CIs) will be reported along with *p* values.

Data analysis will be performed according to the intention-to-treat principle. Participants who withdraw or do not complete the 6-month follow-up will be included in the analysis. A multiple imputation technique will be used for large missing data.

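### Baseline SBP enters the model both as a response and as a covariate, so neither natural reading of the model gives the declared baseline-adjusted 6-month SBP difference

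*Protocol article*

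**What the plan says.** The Primary outcome section states: "The primary outcome is systolic blood pressure at 6-month follow-up adjusted for baseline value". The abstract gives the same definition. This is a comparison conditional on baseline, as in analysis of covariance (ANCOVA).

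The Statistical methods section specifies a "three-level mixed model with random intercepts at both the cluster and the participant-within-cluster levels". Its fixed part is: "The main effects will be group (intervention or comparison), time (baseline, 3 and 6 months) and group × time interaction". Baseline is thus a level of the time factor, and so one of the responses. The same section then says: "Models will be adjusted by baseline value and confounders that include age, gender, body mass index (BMI), duration of hypertension". Baseline is thus also a covariate.

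The responses are not limited to 3 and 6 months, the arms are not constrained to a common baseline mean, and no coefficient is named as the treatment effect. The abstract says that the model "will be used to compare the changes in health outcomes between the intervention and usual care groups", which describes a difference in change.

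**The concern.** A participant's baseline value does not vary over that participant's three occasions. A covariate of that kind shifts all three fitted values equally, so it cancels from any contrast between occasions. The 6-month group × time coefficient is such a contrast. A reader who sees that the model was adjusted for baseline would take this coefficient as baseline-adjusted, and it is not.

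The other reading, group plus interaction at 6 months, does respond to the covariate. Its slope is distorted, however, because one of the three responses is baseline itself, for which the slope is exactly 1.

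Two analysts who follow the text faithfully could therefore report different primary effects, and neither would be the declared one. With ten wards, chance imbalance in baseline SBP is likely enough for the difference to show.

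**Working it through.** **Inputs from the article.** Sample size section: "80% power to detect a difference of 7.3 mmHg SBP between the group means when the standard deviation is 12.1 mmHg", and "five clusters per group with 25 participants per cluster will complete the study and the ICC is 0.05, giving a design effect of 1.48". Statistical methods section: "The level of significance will be set at *p* < 0.05", taken here as two-sided because the article does not say.

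**Inputs assumed.** The correlation ρ between a participant's baseline and 6-month SBP is not given; 0.3, 0.5 and 0.7 are used. The correlation over time of a ward's effect, r, is not given either; 0.5, 0.8 and 1 are used.

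**1. The plan's own figure.** The usual design effect is 1 + (25 − 1) × 0.05 = 2.2. The SE of the difference between arms is 12.1 × √(2 × 2.2/125) = 2.27 mmHg. With a noncentral t on 10 − 2 = 8 df, power for 7.3 mmHg is 80.4%, so the stated 80% is reproduced. (The printed 1.48 equals √2.2. That is a separate matter and does not affect this point.)

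**2. The algebra.** Let D0 and D6 be the differences between arms at baseline and at 6 months.
- Group × time at 6 months: D6 − D0, with or without the baseline covariate when data are complete.
- Group + interaction with the covariate: D6 − b·D0. Here b averages the slopes over the three occasions (1 at baseline, about ρ at each of the other two), so b ≈ (1 + 2ρ)/3.
- ANCOVA, the declared outcome: D6 − ρ·D0.

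For ρ = 0.3, 0.5 and 0.7, b ≈ 0.53, 0.67 and 0.80.

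**3. Check on simulated data.** Three data sets of 10 wards × 25 participants × 3 occasions were fitted by REML with ward and participant intercepts (SD 12.1, ICC 0.05, ρ = 0.5). Estimates are in mmHg.

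| Data set | Interaction without covariate | Interaction with covariate | Group + interaction with covariate | ANCOVA at 6 months | Fitted baseline slope |
|---|---|---|---|---|---|
| No built-in imbalance | −5.950 | −5.950 | −7.40 | −8.22 | 0.67 |
| 5 mmHg imbalance | −12.384 | −12.384 | −10.71 | −9.63 | 0.67 |
| 5 mmHg imbalance, 10% dropout | −13.08 | −13.10 | −11.01 | −9.81 | 0.66 |

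With complete data the interaction is identical in both fits; with 10% dropout it moves by about 0.01. Group plus interaction does move with the covariate (from −10.48 to −7.40 in the first data set) but does not reach the ANCOVA value. In that data set D0 was −4.53, so the predicted gap between interaction and ANCOVA is 0.5 × 4.53 = 2.27, and the observed gap is 8.22 − 5.95 = 2.27.

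**4. Size under chance imbalance.** One SE of baseline imbalance is the 2.27 mmHg of step 1, applying the planning SD and ICC to baseline.
- The interaction differs from ANCOVA by (1 − ρ) × 2.27 = 1.6, 1.1 and 0.7 mmHg for ρ = 0.3, 0.5 and 0.7.
- Group + interaction differs by (1 − ρ)/3 × 2.27 = 0.5, 0.4 and 0.2 mmHg, in the same direction.

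**5. Precision.** The ward variance is W = 0.05 × 12.1² = 7.32 and the participant variance is P = 0.95 × 12.1² = 139.09. For slope b (1 for change, ρ for ANCOVA; ρ is here the within-ward participant correlation):

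Var = (2/5) × [W(1 + b² − 2br) + P(1 + b² − 2bρ)/25]

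At ρ = 0.5 and r = 0.5:
- Change: 0.4 × (7.32 + 5.56) = 5.15, SE 2.27, power 80%.
- ANCOVA: 0.4 × (5.49 + 4.17) = 3.87, SE 1.97, power 90%.

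Power for 7.3 mmHg on 8 df, change v ANCOVA:

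| ρ | r = 0.5 | r = 0.8 | r = 1 |
|---|---|---|---|
| 0.3 | 74% v 86% | 87% v 90% | 95.0% v 92.8% |
| 0.5 | 80% v 90% | 93% v 96% | 98.9% v 98.4% |
| 0.7 | 87% v 93% | 98% v 99% | 99.98% v 99.96% |

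Setting the two variances equal gives r = (1 + ρ)/2 + (P/25W)(1 − ρ)/2, with P/25W = 0.76. The crossover is at r = 0.92, 0.94 and 0.96 for ρ = 0.3, 0.5 and 0.7. Above it, change is slightly more precise; below it, ANCOVA is.

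**The case against.** Three stronger conclusions are tempting, and the article supports none of them.

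- **That the baseline adjustment does nothing to the treatment effect.** This is true only of the interaction coefficient. The article names no primary coefficient, and group plus interaction is a natural reading of an outcome defined at 6 months. The covariate does move that quantity. The accurate statement is that neither reading yields the declared comparison.
- **That the analysis is biased or targets a different effect.** Under randomisation, change and ANCOVA contrasts have the same expected mean difference. What differs is the estimate in the trial at hand when the arms differ at baseline by chance, and its precision.
- **That the trial loses power.** The ward intercept in the planned model is constant over time, which implies r = 1, and there the change contrast is slightly the better one. Even at r = 0.5 with ρ = 0.5 it keeps the planned 80%. Of the combinations tabulated, it falls below 80% only at ρ = 0.3 with r = 0.5. A low ρ is conceivable in patients admitted for uncontrolled hypertension, but the article gives no figure.

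It may also be said that naming the primary coefficient belongs in a statistical analysis plan, which is not shown. That stands for the missing name. It does not cover the double use of baseline, which the article states outright and which conflicts with the outcome it declares.

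**Conclusion.** The point holds as a mismatch between the declared outcome and the stated model. With complete data, the 6-month interaction is an unadjusted difference in change, and it is nearly so with 10% dropout. Group plus interaction is adjusted with a slope pulled towards 1.

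At a one-SE baseline imbalance of about 2.3 mmHg, the interaction departs from the baseline-adjusted estimate by about 0.7 to 1.6 mmHg, or 9% to 22% of the 7.3 mmHg target. This rests on assumed ρ of 0.7 to 0.3 and on the planning SD and ICC holding at baseline.

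The direction of any precision loss depends on how stable ward effects are over time. ANCOVA is better unless that correlation exceeds about 0.92 to 0.96. These consequences are modest and depend on assumptions, so this should be fixed but is not a fatal fault.

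**What to change.** Use baseline SBP once, in one of two ways.

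- **Preferred:** take 3- and 6-month SBP as the responses, with baseline SBP as covariate, group, time, group × time, and ward and participant random effects. Name the group difference at 6 months as the primary contrast.
- **Alternative:** keep baseline as a response, drop it as a covariate, constrain the arms to a common baseline mean, and allow a ward-by-time term so that ward effects need not be constant. Name the same 6-month difference as primary.

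In either case, reword the abstract's sentence on comparing changes to match. Apply the same rule to the other outcomes analysed with this model, since they too are defined at 6 months with baseline adjustment.

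The cost is analysis wording only. No new data are needed, and the change should be recorded before the allocation is revealed to the statistician.

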## Discussion

The transition between hospital care and community care is a critical period in the care of elderly patients with diabetes and hypertension who often have complex medical problems. The incidence rate of adverse events after discharge and the readmission rate are high due to the inappropriate self-care behaviors of patients and lack of timely monitoring of patients’ conditions by health professionals [11, 39]. It has been reported that within a week after hospital discharge, primary health care is required by 80% of patients [11]. Continuity of care through follow-up in primary care as the first contact for patients after discharge can bring positive outcomes for older patients [11, 26]. The transition from passive care to proactive and preventive care can be achieved through establishing a care continuum in the current health systems in China and other low and middle-income countries. Currently, most patients in China only visit doctors when the symptoms of diseases appear. Many complications do not show symptoms in the early stages when they are easier to treat and so the best treatment period may be delayed or missed. By establishing continuous care after discharge, disease-related complications can be prevented or detected earlier and so promptly treated in the primary care system.

As recommended by the World Health Organization [14], patients with chronic conditions require long-term, comprehensive and coordinated care after discharge that is easy to access and provided by the primary health system. A well-developed primary care system contributes to alleviating disparities in healthcare utilization [40]. In 2015, the Chinese government issued an “Outline for the Planning of the National Medical and Health Service System (2015–2020)” which emphasizes collaboration between hospitals and community health service centers. The purpose is to improve prevention and management of chronic disease in primary care settings, reduce hospital care burden and lower national medical costs. This study is in line with these national health reforms that transfer the focus of care from hospitals to community health settings. Interventions introduced in this trial will build capacity of the primary care system to provide accessible and quality care for elderly people with chronic conditions. Interventions in the trial will enable older people to easily access health care a short distance from their home instead of waiting in long queues at a hospital. Collaboration between hospitals and community health service centers can bridge the gap between service capacity of community health professionals and residents’ demand for quality in healthcare.

Hypertension and diabetes management after discharge is a process that requires lifelong adjustments to nonpharmacological and pharmacological interventions due to the chronic nature of these conditions. Lack of adherence to pharmacological and nonpharmacological treatment has been identified as a key barrier to optimal hypertension control. Medication adherence is positively associated with hypertension control and reduction in the risk of complications [41]. However, only 20–60% patients in China comply with antihypertensive drugs [42]. Nearly half of patients with diabetes and hypertension are likely to discontinue their medication treatment in the first 6 months after discharge or when their symptoms diminish [2, 42]. Among the patients who adhere to medications, 50% of them take their medications in an incorrect way [2]. Therefore, long-term medication management is required.

As a chronic disease, hypertension requires life-long medication treatment. Older patients whose memory function decline are more likely to forget taking medications as prescribed and to experience side effects and adverse reactions. Inappropriate medication management can lead to repeat hospital admission. In a study involving 86 patients who were hospitalized, 49% of hospital admissions were due to medical error [11]. Therefore, it is important to prevent medication-related problems. In this study, health professionals at community health service centers will regularly monitor patients’ medication compliance, deal with the side effects of medication and adjust medical therapies to achieve continuity in optimal medication management.

Therapeutic lifestyle changes (TLC) have demonstrated effectiveness in the control of hypertension and improved quality of life among older people [28]. However, a community-based cross-sectional study in Alexandria found that only one in 10 patients can follow the recommended lifestyle modifications such as dietary change, exercise adjustment and weight control [43]. Factors associated with poor self-management include a lack of understanding of the care plan and low confidence and motivation to make healthy choices. Health education can address these barriers by equipping patients with the motivation, self-care skills and knowledge to manage their chronic conditions. Considering the low level of health knowledge among older people, a sustainable and structured follow-up, including regular health education (involving positive behavior changes and medication compliance), and professional health counseling are required for older patients who are discharged. In addition, the monthly monitoring of conditions for older people in community settings can ensure early detection of their functional decline, which prevents hospital readmission. A study in Canada found that hypertension-related hospital admissions of older patients was reduced by 9% during 10 weeks by implementing a community-based education program [42]. Therefore, a sustainable health system is built through promoting service improvements in primary care, such as intensive follow-up to support older patients to maintain their adherence to medical treatment and healthy lifestyle.

Previous hypertension management programs in China have been mostly hospital based or community based and only target either pharmacology or nonpharmacology interventions [8, 26]. This is first trial in China to build integrated care based on collaboration and coordination between hospitals and community health service centers to support older people to manage diabetes and hypertension at home using multifactorial interventions. In addition, this study synthesizes the latest evidence and includes the combination of effective intervention components on hypertension management for people with diabetes, which differs from the previous studies in China that only tested single intervention components [44, 45].

The program, if effective, will have an immediate application to hypertension management in the healthcare system in China. In addition, this study uses hypertension and diabetes as an entry point to improve chronic disease management in primary care. Success of this intervention program, that transfers patients from hospital to community health service centers, can also be applied to the management of other chronic diseases for hospitalized patients.

Limitations of this study are the following. First, the trial will be undertaken in 10 clusters only and hence sampling bias may occur, which means that the findings may not represent the population. Second, as an open-label study, the patients and health professionals will be aware of the groups they are assigned to and their allocated treatment during the trial. Patient bias may occur when they complete the self-reported questionnaires. Third, the duration of follow-up at the community health service center is relatively short (only 6 months). The long-term effects of this intervention program will need to be explored in a future study.

## Trial status

At the time of submission of the manuscript, this trial is in progress and participants are being recruited. The study began in June 2017, and is expected to be complete by June 2018.

## Abbreviations

GP: General practitioner
HbA1C: Glycosylated hemoglobin
